### Analysis plan

Differences in patient characteristics in primary care versus secondary care will be presented using suitable numerical and graphical summaries. A nonlinear mixed model for a binomial response will be used to compare the proportion of uptake between those in primary and secondary care while adjusting for differences in patient characteristics at baseline as appropriate. The analysis of the secondary responses will involve linear and nonlinear mixed models for continuous and categorical responses and survival models for the analysis of time to event data. The main analysis will follow an intention-to-treat strategy; sensitivity analyses and per protocol analysis will be used to explore the effect of departures from the assumption made in the main analysis. All analyses will be performed using R Statistical advice and analysis will be provided by [name] of the HRB Clinical Research Facility, NUI Galway.

### Study management

A study management group will be formed comprising the principal investigator, co-investigators and trial statistician. A data monitoring committee is not required as the study management group will liaise every month to review interim analysis and monitor adherence. The principal investigator will make the final decision to terminate the trial in the event that uptake rates fall below pre-trial levels in either intervention arm. It is not anticipated that there will be premature termination of study. However, if this occurs, then the data will be analysed and results circulated to team members. The ethics committee will be notified of premature termination and the reasons for termination. Adverse events or other unintended effects of trial interventions that come to the attention of trial investigators will be reported immediately to the study management Group. All protocol amendments will be submitted to the ethics committee for review and approval before implementation and to trial registries.

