**Methods/Design:**

This will be an unblinded, two-group, parallel randomised controlled trial (RCT). The target population includes 784 women presenting for their first antenatal visit at 12 to 18 weeks gestation at two hospitals in the west of Ireland: Galway University Hospital and Mayo General Hospital. Participants will be offered universal screening for GDM at 24 to 28 weeks gestation in either primary care (n = 392) or secondary care (n = 392) locations. The primary outcome variable is the uptake rate of screening. Secondary outcomes include indicators of clinical effectiveness of screening at each screening site (primary and secondary) including gestational week at time of screening, time to access antenatal diabetes services for women diagnosed with GDM, and pregnancy and neonatal outcomes for women with GDM. In addition, parallel economic and qualitative evaluations will be conducted. The trial will cover the period from the woman’s first hospital antenatal visit at 12 to 18 weeks gestation, until the completion of the pregnancy.

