### Interventions

All women who consent to participate in the study will be invited for a 2-hour, 75 g, oral glucose tolerance test (OGTT) at between 24 to 28 weeks gestation. Participants will be randomised into either the primary care screening group or the secondary care screening group. The scheduling process differs slightly between groups. In the primary care group, the GP is requested to schedule the OGTT screening appointment with the woman; in the secondary care group researchers schedule the screening appointment during the recruitment phone calls. In neither group is the responsibility for scheduling the appointment left to the woman.

Primary care screening group: All women randomised to the primary care screening group will be offered a screening appointment for GDM at their local general practitioner (GP) clinic. Following randomisation, a study information leaflet and the materials required to perform an OGTT will be sent to the woman’s GP by the research team. The GP is requested to contact the woman in order to schedule the OGTT appointment at 24 to 28 weeks gestation. As per usual care, the GP will send the test samples to the local laboratory for analysis. Following analysis, the laboratory will send the test results directly to the GP and the GP will inform the woman of her result. For positive test results, the GP will be directed to contact the local maternity unit to make an appointment for the woman to be seen at the diabetes antenatal service.

Secondary care screening group: All women randomised to the secondary care screening group will be offered a screening appointment at the hospital site. Following randomisation, the study researcher will schedule the appointment for the OGTT screen and send the list of OGTT appointments to the maternity unit, for inclusion in their OGTT appointment diary. As per usual care, the test samples will be sent to the local laboratory for analysis. Following analysis, the laboratory will send the test results directly to the consulting obstetrician, who in turn informs the woman of her result. For positive test results, an appointment will be made by the midwife for the woman to attend the antenatal diabetes service.

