#### Recruitment

Recruitment for the trial will be initiated at the woman’s first hospital visit at 12 to 18 weeks gestation. A list of all women with a confirmed pregnancy presenting at the obstetrics outpatient clinics at GUH and MGH will be obtained from the hospital databases by the principal investigator, who is a member of the clinical care team at both sites. Each woman will be sent an invitation letter, participant information leaflet and participant consent form in the post. The information will be followed up with a phone call to each woman to answer questions and obtain verbal consent before randomising those who consent to the primary care and secondary care screening groups. The baseline characteristic questionnaire will be administered at this time. The phone calls will be conducted by members of the research team. Each consenting woman will be asked to return the written consent form to the study office. For some of the participants (that is, those who meet the risk factor criteria for selective GDM screening), an appointment for an OGTT may have already been scheduled at their 12 to 18 week hospital visit. In such cases, researchers will continue the randomisation process as usual and inform the clinic if a change is required to the screening schedule. Those who were not selected for screening at the 12 to 18 week clinic but who consent to the study and are randomised into the secondary care screening group will be added to the hospital’s screening schedule. Outcome data will not be collected from participants who discontinue. The flow chart in Figure 1 represents the movement of a participant through the stages of recruitment.

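### Monthly interim review by the investigators of an unblinded trial implies sight of uptake by arm, and a response to the lagging arm could dilute a true difference

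*Protocol article*

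**What the plan says.** All of the following is in the Protocol article.

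- **Who reviews, and how often** (Study management): "A study management group will be formed comprising the principal investigator, co-investigators and trial statistician". The next sentence reads: "A data monitoring committee is not required as the study management group will liaise every month to review interim analysis and monitor adherence".
- **What they act on** (Study management): the principal investigator takes the final decision to terminate "in the event that uptake rates fall below pre-trial levels in either intervention arm".
- **Blinding** (Abstract and Methods/Design): the trial is unblinded.
- **Who arranges attendance** (Interventions): "in the secondary care group researchers schedule the screening appointment during the recruitment phone calls". In the primary care group the research team sends the GP the leaflet and test materials, and the GP is asked to arrange the test.
- **Who recruits** (Recruitment): "The phone calls will be conducted by members of the research team". The list of women "will be obtained from the hospital databases by the principal investigator, who is a member of the clinical care team at both sites".
- **What is measured** (Primary outcome): uptake is the number of OGTTs done, from laboratory records, over the number of women randomised to that setting.

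**The concern.** The section does not say what the interim analysis contains. However, a trigger that concerns uptake in either arm cannot be applied without uptake by arm, and that is the primary outcome. In a screening-uptake trial, monitoring adherence also comes close to monitoring that same outcome.

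The laboratory record protects the measurement of attendance but not attendance itself, which depends on whether a slot is booked, kept or rebooked and whether a GP acts on the request. The people who direct the trial would know each month which arm is behind. The termination rule also gives them a reason to lift an arm that is falling. The envelope concealment under Randomisation protects the allocation sequence only until assignment, and does nothing afterwards.

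At stake is the contrast the trial exists to estimate. If the lagging arm receives extra prompting because it lags, the observed difference understates the difference between settings. The extra contact comes after randomisation, so adjusting for baseline characteristics (Analysis plan) cannot remove its effect.

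**Working it through.** **Inputs from the article.** 784 women, 392 per arm, 80% power, 5% significance and a change of at least 10% in uptake (Sample size and power calculation; Abstract). Earlier uptake was 44% (Background). Enrolment runs from January 2013 to December 2014, about 24 monthly meetings (Trial status). Entry is at 12 to 18 weeks and testing at 24 to 28 weeks.

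**Assumptions.** The 10% change is read as 10 percentage points, the test as two-sided, and 44% as the base rate; the sample-size paragraph states none of these. The conversion rate c, the share of the lagging arm's non-attenders who attend because of extra contact, is set at 5% and 10%. No figure for c is in the article.

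**1. The plan's own figure.** For 44% against 54%, the mean is 49%:

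n = [1.96 × √(2 × 0.49 × 0.51) + 0.8416 × √(0.44 × 0.56 + 0.54 × 0.46)]² / 0.10² = 391.1, so 392 per arm and 784 in all. This reproduces the plan.

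**2. A simple bound.** Suppose the arm at 44% is chased from first woman to last. Its uptake becomes 0.44 + c × 0.56. Power is approximately Φ[(d − 1.96 × s0)/s1], where d is the difference and s0 and s1 are the pooled and unpooled standard errors at 392 per arm.

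- No chasing: d = 0.100, (0.100 − 0.0700)/0.0355 = 0.845, power 80%.
- c = 5%: uptake 46.8%, d = 0.072, (0.072 − 0.0700)/0.0356 = 0.056, power 52%.
- c = 10%: uptake 49.6%, d = 0.044, (0.044 − 0.0700)/0.0357 = −0.73, power 23%.

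**3. The reactive version, by simulation.** There are 24 monthly cohorts totalling 392 per arm. Each month the arm with lower cumulative uptake gets conversion rate c in its next cohort, with results seen either at once or three months late. The lag matters because uptake trails entry by 24 − 18 = 6 to 28 − 12 = 16 weeks.

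| True uptake | c | Rejection rate, results at once | Three months late |
|---|---|---|---|
| 44% v 54% | 5% | about 57% | about 60% |
| 44% v 54% | 10% | about 30% | about 37% |
| 44% v 44% | 5% | 0.9% | 1.2% |
| 44% v 44% | 10% | 0.1% | 0.2% |

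Repeat runs agree to about one point in the first two rows. Without chasing, the simulation gives 80% and 5%, as it should. The last two rows show that helping whichever arm is behind pulls the arms together and makes false positives rarer.

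**The case against.** The strongest reply is that the article describes no chasing at all. Interventions gives one booking action per arm, after which the maternity unit's diary or the GP practice takes over. Reminder schedules and data-access rules are also details that a journal article usually leaves to the full protocol. This stands in part. It makes the point a risk and not a described bias, and the conversion rates remain assumptions. It does not remove the point, because the article positively states who reviews interim results, how often, and that this takes the place of a monitoring committee.

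An unblinded screening trial without a data monitoring committee is not wrong in itself, and that also stands. The weakness is who sees uptake by arm, not the absence of a committee.

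A reader might infer several stronger things that the documents do not support:

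- **That false positives would rise to about 35%.** That figure comes from comparing 44% with 44% + 0.10 × 56% = 49.6% at 392 per arm (rejection probability 0.349). It requires one fixed arm to be boosted throughout when there is no true difference, which is not a reaction to whichever arm lags.
- **That effort in the consent calls could favour an arm.** Verbal consent is obtained before randomisation (Recruitment) and the sequence is concealed until assignment (Randomisation).
- **That the callers and bookers sit on the reviewing group.** The text does not say so. The principal investigator's one stated recruitment task is obtaining the list of women.
- **That there are 24 full opportunities to react.** The delay of 6 to 16 weeks leaves the earliest meetings with little uptake to see. The three-month column allows for this, and the loss of power is only somewhat smaller.

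**Conclusion.** The point holds as a conduct risk of moderate size. Study management places monthly interim review with the people who run an unblinded trial. The termination trigger implies that they see the primary outcome by arm, and that outcome can be moved by contact after randomisation.

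The expected direction is dilution of a true difference. With 5% to 10% of the lagging arm's non-attenders converted, power for 44% against 54% falls from 80% to roughly 60% to 30%. This rests on the assumed conversion rates, on monthly reaction throughout recruitment, and on reading interim analysis as including uptake by arm. If no one reacts, nothing is lost. The case for acting is that the change is cheap and that the damage, if it occurred, could not be repaired in the analysis.

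**What to change.** Amend Study management as follows.

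1. The monthly group sees recruitment, adherence to trial procedures and uptake pooled over the arms, and nothing by arm.
2. Uptake by arm goes only to a statistician who has no contact with women or GPs. That person tells the group only whether the termination limit has been crossed. The limit therefore has to be written down beforehand as a definite figure. The principal investigator keeps the final decision.
3. Contact, rebooking and reminder procedures for women and GPs are fixed in advance for both arms and are not changed in response to interim uptake.
4. The covariates of the primary model are fixed before anyone looks at uptake by arm. The Analysis plan adjusts for baseline differences as appropriate, and the statistician who sees the arms may also carry out the final analysis.

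The cost is a wording amendment submitted to the ethics committee, with no new staff. The drawback is that the investigators lose the monthly by-arm view and would learn of a problem confined to one arm only through the statistician's report.

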In terms of screening, for example, professional groups disagree on whether to recommend universal or selective screening (based on risk factors) [12,18,19]. While some studies have found that universal screening for GDM is superior to risk factor-based screening in terms of number of cases detected, time to diagnosis and treatment, and improved pregnancy outcomes [20,21], others have found no such effects. For example, a review of four trials comparing universal and selective screening, found that there is little high-quality evidence on the effects of screening for GDM on health outcomes for mothers and their babies. The paper concluded that further research is required to see which recommendations for screening practices for GDM are most appropriate [22].

Additionally, the site of screening is likely to be important, both in terms of the location of the screen (regional versus local) and in terms of the provider of the screening service (GP versus hospital). For example The Atlantic DIP study, which offered universal screening to all pregnant women, recorded an uptake rate of only 44% [17]. Follow-up analysis to explain this low screening uptake rate revealed that travel distance to the hospital screening site is an important factor in determining uptake rates [23]. Specifically, the probability of attending for screening is 15% lower for a patient who lives 50 kilometers from a screening centre, compared to an otherwise similar patient who lives closer to the hospital. The corresponding reduction in the probability of attending for an individual residing 100 kilometers away is 30%. This suggests that the availability of GDM screening in local (primary care) settings could result in higher uptake rates; however, this has not been empirically tested to date.

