#### Sample size and power calculation

On the basis of a comparison of two proportions a sample of 784 is needed to have 80% power, at the 5% significance level, to detect a ≥10% change in screening uptake. To achieve the required sample size, 1,513 patients will be invited to participate in the RCT, as 74% recruitment and 30% patient attrition (seen in Atlantic DIP) is anticipated. Recruitment will continue until target sample size is reached.

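### The termination criterion on the primary outcome has no reference figure, margin, minimum number or interim denominator, covers the arm in the existing setting, and is not reflected in the power calculation

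*Protocol article*

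**What the plan says.** The Study management section dispenses with a data monitoring committee because "the study management group will liaise every month to review interim analysis and monitor adherence". The group consists of the principal investigator, the co-investigators and the trial statistician. The principal investigator takes the final decision to "terminate the trial in the event that uptake rates fall below pre-trial levels in either intervention arm". The same section adds that early termination is not expected.

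Uptake is the primary outcome (Outcomes). Its rate is defined as OGTTs performed over women randomised to that setting. No number is attached to the pre-trial level. The only earlier uptake figure is in Background: the Atlantic DIP study, which offered screening to all pregnant women, "recorded an uptake rate of only 44" per cent.

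The sample size section states that "a sample of 784 is needed to have 80% power", "to detect a ≥10% change in screening uptake". It mentions neither the interim reviews nor the termination criterion. The Abstract splits the target into "either primary care (n = 392) or secondary care (n = 392) locations".

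Screening in Ireland says that hospital sites are the only current place of GDM screening. In the trial, however, "in the secondary care group researchers schedule the screening appointment during the recruitment phone calls". Under Recruitment, women whom the clinic had not picked for screening are added to the hospital schedule.

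**The concern.** A rule that compares an observed proportion with a fixed level, with no margin or minimum number, responds to noise. The secondary-care arm uses the existing setting. If its true uptake is near the reference, its observed rate lies below the reference about half the time at any one look, and monthly looks give it many chances to do so.

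Three further weaknesses follow from the text:

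- **Purpose.** The null hypothesis is equal uptake. Low uptake in one arm is one of the answers the trial is designed to give.
- **Comparability.** The 44% is a share of all women offered screening. Trial uptake is a share of women who consented and were randomised.
- **Timing.** Women are recruited from the 12 to 18 week visit, but the OGTT is at 24 to 28 weeks. If all randomised women form the denominator, early looks show artificially low uptake in both arms.

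At stake are the chance of finishing the trial, its power, and an unbiased estimate, since stopping would depend on an arm being observed low.

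**Working it through.** **Inputs from the protocol article.** 80% power; 5% significance; 10-point change; 392 per arm; enrolment January 2013 to December 2014, so about 24 monthly looks and 392/24 ≈ 16 women per arm per month.

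**Assumptions.** The change is absolute and the test two-sided. The reference is 44%, because it is the only prior uptake figure given. Accrual is even, and each woman's result is known at the look.

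**Step 1: reproduce the plan's figure.** With p1 = 0.44, p2 = 0.54 and mean 0.49,

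n per arm = [1.96·√(2·0.49·0.51) + 0.842·√(0.44·0.56 + 0.54·0.46)]² / 0.10² = (1.386 + 0.592)² / 0.01 ≈ 391.1, rounded up to 392.

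The total is 784, as stated. A control rate of 45% also gives 784. A control rate at the 44% reference is therefore consistent with the trial's own sample size, although that section states no control rate.

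**Step 2: a single look.** With 392 women and true uptake 44%, P(at most 172 tested) = 0.50, where 172/392 = 43.9%.

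**Step 3: repeated looks.** Simulation of cumulative uptake at 24 equal looks, stopping at the first look where either arm is below 44%, then a two-proportion z test at 5% on the data at that point. Primary-care uptake is 10 points above control throughout.

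| True control uptake | Rule from 65/arm: fires | Power | No minimum: fires | Power |
|---|---|---|---|---|
| 44% | 83% | 40% | 93% | 20% |
| 49% | 35% | 70% | 66% | 40% |
| 54% | 7% | 80% | 39% | 59% |
| 60% | 0.6% | 84% | 17% | 75% |

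In the first row, from 65 per arm, the mean size at the end is about 146 per arm and the effect is overstated by about 2 points. If the rule is used only from 196 per arm, it fires in 71% of trials (power 69%) at 44% control and in about 12% (power 80%) at 49%.

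**Step 4: the denominator.** From the hospital visit, the OGTT comes between 24 − 18 = 6 and 28 − 12 = 16 weeks later. Take the mid-range, 11 weeks or about 2.5 months, as an illustration. With all randomised women as denominator, an arm with true uptake 54% shows about 0.54·(m − 2.5)/m at month m. That is 0.54·10.5/13 = 43.6% at month 13 and 0.54·11.5/14 = 44.4% at month 14. On that reading even the better arm sits below 44% for about the first 13 months. Step 3 leaves this lag out.

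**The case against.** The strongest reply is that the scenario is unfavourable by choice. Consent, an offer to every participant and researcher-made bookings may all lift hospital uptake above 44%, and the table shows how quickly the problem then shrinks. This stands: the large figures hold only when control uptake is close to the reference. For the same reason, a reader might infer that the secondary-care arm simply is pre-trial practice. That is true of the setting, but not of who is offered screening, who is counted or how the test is booked.

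Second, the decision is discretionary. The criterion permits termination and does not compel it, so a reader who infers that stopping is near certain, or that 80% power is lost outright, goes further than the document. This also stands. It does not supply the missing reference or margin, and it leaves an open-ended judgement on the primary outcome to an investigator in an unblinded trial.

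Third, a reader might infer that the people who recruit and book appointments see results by arm. The criterion cannot be applied without by-arm figures, but the article does not say that the management group and the callers are the same people. Nor does it propose efficacy testing at the monthly reviews, so inflation of the false-positive rate through repeated testing is not part of this point.

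Fourth, an article condenses its full protocol. That would excuse silence on interim monitoring. Here the article itself states the termination criterion, and states it in a form that cannot be applied consistently.

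Finally, a floor on uptake may have a protective purpose. That supports defining it properly, not leaving it as it is.

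**Conclusion.** The point holds in conditional form. The article fixes a termination criterion on the primary outcome that lacks a reference figure, margin, minimum number and interim denominator, and the power calculation takes no account of it. If secondary-care uptake is close to the reference, mechanical use would stop about 83% of trials (from 65 per arm) to 93% (no minimum), with power of about 40% and 20% instead of 80%. This rests on a 44% threshold, 24 looks, even accrual and action on every dip. The figures are upper bounds because the decision is discretionary, and the risk becomes small once control uptake is well above the reference, provided very early looks are not acted on. The mismatch between the 44% and trial uptake, and the lag between randomisation and OGTT, are defects of the criterion whatever the control rate is.

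**What to change.** Delete observed by-arm uptake as a termination trigger. Limit the monthly review to pooled recruitment, data completeness, adherence and adverse events.

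If a floor is kept, the trial statistician alone should check it once, at half the randomised women, counting only women past 28 weeks, against a stated numerical reference. The trial should stop only if the upper 95% confidence limit of an arm lies below that reference. No pre-trial rate among randomised women is given, so the reference has to be chosen and justified, and its different denominator acknowledged.

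As an illustration with a 44% reference and 196 women per arm: 72/196 = 36.7% has upper limit 0.367 + 1.96·√(0.367·0.633/196) = 43.5%, whereas 73/196 gives 44.0%, just above the reference. Stopping therefore needs 72 or fewer tested, which has probability 0.023 when true uptake is 44%.

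The cost is protocol wording only, with no new committee. The downside is that the management group does not see by-arm uptake during the trial, so a scheduling failure confined to one arm would be noticed later.
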